#### Sample size and power calculation

2.7.1

The sample size for this trial was calculated using ‘pwr.t.test’ (for a Student t-test) in the ‘pwr’ package in R statistical software (70). The required sample size was estimated to ensure at least 80% power, with a two-sided alpha significance level of 5%, to detect clinically important effects of the two factors THC and CBD, on spasticity, which is the primary outcome (71). A target total recruitment of 200 patients would cover scenarios with a mean change from baseline among treated patients ranging from −1.90 to 1.55, where −1.55 is what we consider to be the minimal clinically significant effect (22, 33, 72, 73). However, some power would be lost upon Bonferroni adjustment. Thus, a target total recruitment of 250 patients would be more adequate, after accounting for a potential rate of attrition of 5% over the study period, based on previous studies (22, 33, 72, 73) and the clinical experience at the CHUM MS Clinic.

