**Methods:**

A double-blinded, randomized, factorial, placebo-controlled trial will be performed. We intend to include up to 250 PwMS aged over 21 recruited from the Centre hospitalier de l’Université de Montréal MS Clinic. PwMS will be randomly assigned on a 1:1:1:1 ratio to one of the trial arms: THC alone, CBD alone, THC/CBD combination, or placebo, using stratified blocked randomization, with random blocks within each stratum. The primary outcome is a self-assessment of spasticity using the mean Numeric Rating Scale score over 7 days. The main outcome will be the difference in this score at 4 weeks compared to baseline. Secondary outcomes include assessments of spasticity as measured by a clinician, pain, fatigue, sleep, bowel, bladder, and sexual dysfunction, restless legs syndrome, mental health, quality of life, mobility, cognitive functioning, and adverse events. Treatment responders are eligible for a 12-week extension phase, using the same treatment allocation and assessments.

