#### Primary endpoints

2.7.2

Firstly, an analysis of variance (ANOVA) will be used to assess the treatments effect on the differences in the mNRS from baseline to week 4. The normality of the responses will be assessed using normal-quantile plots. The ANOVA model will only include the factors THC and CBD. Secondly, an analysis of covariance (ANCOVA) will be used to evaluate the treatments effect on the post-intervention mNRS while adjusting for baseline mNRS and sex (stratification variables). The ANCOVA may reduce potential bias present in the ANOVA model (74). Finally, the ANCOVA model described above will be expanded by including potential confounders, such as biomarkers, for which a clinically meaningful difference between any two groups will be revealed by the preliminary descriptive analysis. The estimated adjusted and unadjusted differences in mNRS from baseline to week 4 and their 95% confidence intervals will be reported for all models.

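### Holm's step-down adjustment could replace Bonferroni over the THC and CBD tests: same 5% family-wise error, more power if both drugs work, no extra patients

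*Protocol article*

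**What the plan says.** Section 2.7.1 of the protocol article bases the sample size on a two-sample t-test with a two-sided 5% level. On power it says: "The required sample size was estimated to ensure at least 80% power". The targets are two effects; the calculation is meant "to detect clinically important effects of the two factors THC and CBD, on spasticity". A total of 200 is said to cover the planned effects. The text continues: "However, some power would be lost upon Bonferroni adjustment". The target then becomes 250, which also allows for 5% attrition.

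Section 2.7.2 tests both factors in one main-effects model: "The ANOVA model will only include the factors THC and CBD". It promises 95% confidence intervals for all models and names no multiplicity procedure. Bonferroni, in 2.7.1, is the only multiplicity method in the article. The tests it is meant to cover are not listed.

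**The concern.** With two hypotheses, Bonferroni tests each at 0.025. Holm tests the smaller p-value at 0.025 and, if that is significant, the larger at 0.05. Holm rejects everything Bonferroni rejects and sometimes more, with the same strong control of the family-wise error.

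The difference matters most when both drugs work, and that is what the trial expects: section 1.1 hypothesises relief from THC alone, CBD alone and the combination. Once one drug has been shown, Bonferroni still holds the other to 0.025 although the error rate does not require it. The plan pays for this partly with recruitment, so power that needs no patients is worth having.

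**Working it through.** **Inputs.** From 2.7.1: two-sided alpha 0.05, power 80%, two-sample t-test, 200 patients before adjustment, 250 after adjustment and 5% attrition. From 2.7.2: two factors, no interaction term. From the abstract: "PwMS will be randomly assigned on a 1:1:1:1 ratio to one of the trial arms". Each factor therefore compares one half of the sample with the other half, and the two contrasts are orthogonal. Not given: the standard deviation and the placebo change.

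**Assumed effect.** Solving the t-test for 100 against 100, alpha 0.05 and power 0.80 gives d = 0.398.

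**Does the step to 250 fit two tests?** Re-solve for 80% power at 0.05/k, then divide by 0.95:

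| k | Evaluable | Recruited |
|---|---|---|
| 2 | 242 | 255 |
| 3 | 267 | 281 |
| 4 | 285 | 300 |

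Two tests come within about 2% of the stated 250; three or four do not. If the 200 already included attrition, two tests give 242 recruited, which is also close. The arithmetic supports a two-test family, but that remains an inference.

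**Power at 250 × 0.95 = 237.5 analysed, d = 0.398 for both drugs.** Let b be the power at 0.025 and a the power at 0.05. The non-central t gives b = 0.7911 and a = 0.8633, so a − b = 0.0722 (0.07227 unrounded).

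- Bonferroni, per drug: b = 0.791.
- Holm, per drug: b + (a − b)·b = 0.7911 + 0.0722 × 0.7911 = 0.848, a gain of 5.7 points.
- Bonferroni, both drugs: b² = 0.626.
- Holm, both drugs: a² − (a − b)² = 0.7453 − 0.0052 = 0.740, a gain of 11.4 points.
- At least one drug, either method: 1 − (1 − b)² = 0.956.
- Only one drug effective: the gain for it is (a − b) × 0.025 = 0.0018, about 0.2 points.
- Evaluable patients for 80% per drug: 242 under Bonferroni; 212 under Holm if both drugs have this effect.

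**Simulation.** The 2×2 main-effects ANOVA with 236 patients and 200,000 runs gave 78.8% and 84.6% per drug, and 62.2% and 73.6% for both. With neither drug effective, the family-wise error was 4.9% under both methods. With one drug effective, Holm's error on the null drug was 4.5%.

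**Sensitivity.**

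| Analysed | d | Per drug, Bonferroni to Holm | Both, Bonferroni to Holm |
|---|---|---|---|
| 237.5 | 0.398 | 79.1% to 84.8% | 62.6% to 74.0% |
| 250 | 0.398 | 81.3% to 86.8% | 66.1% to 77.0% |
| 237.5 | 0.488 | 93.3% to 96.1% | 87.1% to 92.6% |

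The value 0.488 is 0.398 × 1.90/1.55. It assumes that 0.398 belongs to a change of −1.55, that placebo change is zero, and that the range in 2.7.1 runs from −1.90 to −1.55. The 250 row reflects sections 2.7 and 2.7.5, which keep all randomised patients and fill a missing outcome with the baseline value. It ignores the dilution that such filling causes.

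**The case against.** The strongest reply is that nothing here is wrong. Bonferroni is valid and keeps the 5% error rate. Its one mention sits in a sample-size argument, the family is not spelled out, and the analysis section names no procedure. Sizing for Bonferroni does not prevent a step-down test in a statistical analysis plan that is not shown. This stands as a limit on the point: a reader might infer a mistake or a loss of error control, and the article supports neither. It does not remove the point, because Bonferroni is the only method named and the target was raised partly for it.

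The second reply is that Bonferroni has simple matching intervals. That is a real advantage. Holm adds a rejection only when the larger p-value lies between 0.025 and 0.05 and the smaller is below 0.025. In exactly those cases the 97.5% interval for the second drug includes zero. The reporting must deal with this openly.

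The third reply is that the headline gain is a favourable case. It rests on a back-solved effect and on both drugs working, and it shrinks for larger effects. That also stands. Nor is it a ceiling: at 237.5 analysed with equal effects, the gains peak at 6.4 and 12.8 points, near d = 0.345.

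**Conclusion.** The point holds as a low-cost improvement. Holm gives the same strong 5% family-wise control as Bonferroni, needs no extra assumption and is never less powerful. If the family is the two factor tests, both drugs have d = 0.398 and about 237 are analysed, the gain is about 6 points per drug and 11 points for showing both. It falls to about 3 and 6 points at d = 0.488 and almost vanishes if only one drug works. The chance of showing at least one drug is the same under either method.

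Two stronger readings should be resisted. A reader might infer that 250 is inadequate under Bonferroni, but under these assumptions power per drug is about 79% to 81%, essentially at target. A reader might also infer that recruitment could be cut to the Holm figure. That figure requires both drugs to have the planning effect, which the trial cannot presume.

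**What to change.** In 2.7.1, replace the Bonferroni wording with Holm adjustment over the THC and CBD tests, which also states the family. In 2.7.2, where there is no multiplicity wording to replace, add a sentence: in the primary model, the smaller of the THC and CBD p-values is tested at 0.025 and, if it is significant, the larger is tested at 0.05.

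Keep the recruitment target. Restate power under Holm for two cases: both drugs effective, and one drug effective.

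For reporting, make the Holm-adjusted p-values the basis of the decision and label the planned 95% intervals as unadjusted. State that a simultaneous 97.5% interval may include zero for a drug declared effective at the second Holm step.

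The cost is a few sentences, fixed before unblinding, and no patients. What is given up is the simple match between test and interval that Bonferroni offers.

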#### Primary endpoints

2.7.2

Firstly, an analysis of variance (ANOVA) will be used to assess the treatments effect on the differences in the mNRS from baseline to week 4. The normality of the responses will be assessed using normal-quantile plots. The ANOVA model will only include the factors THC and CBD. Secondly, an analysis of covariance (ANCOVA) will be used to evaluate the treatments effect on the post-intervention mNRS while adjusting for baseline mNRS and sex (stratification variables). The ANCOVA may reduce potential bias present in the ANOVA model (74). Finally, the ANCOVA model described above will be expanded by including potential confounders, such as biomarkers, for which a clinically meaningful difference between any two groups will be revealed by the preliminary descriptive analysis. The estimated adjusted and unadjusted differences in mNRS from baseline to week 4 and their 95% confidence intervals will be reported for all models.

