
### Randomization

2.4

Patients who meet all the inclusion criteria and none of the exclusion criteria and consent to take part in the trial after they have received the study oral and written information, will then be randomly assigned in equal proportions to either THC, CBD, THC + CBD, or placebo using stratified block randomization. Randomization will be stratified by sex and baseline mean spasticity score. In each of the 4 strata, corresponding to different combinations of sex (male vs. female) and baseline mean spasticity score ([2-6[vs. ≥6), randomization will be performed using blocks of size 4. This will minimize the imbalance between group sizes, while preventing unblinding of the treatment allocation of consecutive participants. The randomization schedule will be generated by CHUM’s Centre for the Integration and Analysis of Medical Data (CITADEL), who will send the randomization codes to the CHUM research pharmacy and keep secure digitalized copies. Randomization codes will be maintained throughout the study.

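### Section 2.7.2 lists an unadjusted change-score ANOVA first among three primary-endpoint models, names none as decisive, and does not carry over the Bonferroni adjustment used in sizing

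*Protocol article*

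**What the plan says.** Section 2.4 (Randomization): "Randomization will be stratified by sex and baseline mean spasticity score", in blocks of four within four strata.

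Section 2.7.2 (Primary endpoints) sets out three models in order:
1. "Firstly, an analysis of variance (ANOVA) will be used to assess the treatments effect on the differences in the mNRS". The only terms are THC and CBD.
2. An ANCOVA of post-treatment mNRS adjusting for baseline mNRS and sex. The section identifies these as the stratification variables and says that adjustment may reduce bias present in the ANOVA.
3. The same ANCOVA with further covariates, such as biomarkers, chosen because the descriptive analysis shows the groups to differ on them.

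The section closes: "The estimated adjusted and unadjusted differences in mNRS from baseline to week 4 and their 95% confidence intervals will be reported for all models". It does not say which model decides the trial. The section headed Sensitivity analysis (2.7.6) covers only the interaction model, so the ANOVA and the expanded ANCOVA are not given a supportive role there.

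Section 2.7.1 (Sample size and power calculation) states the error rate and target: "The required sample size was estimated to ensure at least 80% power", "with a two-sided alpha significance level of 5" per cent, "to detect clinically important effects of the two factors THC and CBD, on spasticity, which is the primary outcome". It arrives at 200 patients and adds: "However, some power would be lost upon Bonferroni adjustment". It then moves to 250, also allowing 5% attrition. It gives neither the number of tests nor the adjusted level.

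**The concern.** Two parts of the plan do not fit together.

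- **Design and first model.** Stratified allocation balances the arms on sex and baseline spasticity. A model that leaves both out keeps their variation in the residual, so its standard errors are too wide and its test is conservative. It also gives up the precision that the baseline measurement offers. The plan lists this model first, while saying that the second one may be less biased.
- **Sizing and analysis.** Part of the increase from 200 to 250 is attributed to a Bonferroni adjustment. The analysis text then gives 95% intervals throughout and no adjusted level.

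At stake is whether the trial has one pre-stated answer. If the ANOVA and an ANCOVA fall on opposite sides of the threshold, the text does not say which result stands or at what level each factor is judged.

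**Working it through.** **Inputs from the article.** Two-sided 5% and 80% power; two factors; 200 patients before adjustment, 250 after; 5% attrition (all 2.7.1). Equal allocation to four arms, so about half the patients are at each level of each factor (2.4).

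**Inputs not given.** The SD of change, the placebo change and the baseline-to-week-4 correlation (rho). The stated effect is a "mean change from baseline among treated patients ranging from −1.90 to 1.55" (the second sign is printed as positive), and that alone does not reproduce 200. I therefore assume that 200 gives exactly 80% per factor (100 against 100, a standardized difference of 0.398 SD of change) and take rho from 0.3 to 0.9.

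**Step 1: what the move from 200 to 250 implies.** For k tests the multiplier is ((z(1−0.05/2k) + 0.842)/(1.960 + 0.842))², followed by division by 0.95.

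| k | multiplier | evaluable | after 5% attrition |
|---|---|---|---|
| 1 | 1.000 | 200 | 211 |
| 2 | (3.083/2.802)² = 1.211 | 242–243 | 255–256 |
| 3 | (3.236/2.802)² = 1.334 | 267–268 | 281–283 |

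Only k = 2 comes close to 250 (within 3%). The target is consistent with 0.025 for each of two factors.

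**Step 2: precision.** With equal variances at both visits, var(ANCOVA)/var(change score) = (1 − rho²)/(2(1 − rho)) = (1 + rho)/2. Power is from the two-sample t-test at 0.025 with 250 × 0.95 = 237 evaluable. The ANCOVA effect size is 0.398/√((1 + rho)/2).

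| rho | variance ratio | ANOVA power | ANCOVA power | evaluable N for 80%, ANCOVA |
|---|---|---|---|---|
| 0.3 | 0.65 | 79% | 94% | 158 |
| 0.5 | 0.75 | 79% | 90% | 182 |
| 0.7 | 0.85 | 79% | 86% | 206 |
| 0.9 | 0.95 | 79% | 81% | 230 |

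The ANOVA needs 242 evaluable.

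**Step 3: error rates under stratified allocation.** Null simulation with 236 patients, blocks of four within sex by baseline strata, and 6,000 runs per rho. Assumptions: baseline split at its centre; for the third model, six candidate covariates explaining 30% of residual variance, added when any two arms differ by more than 0.4 SD.

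| At nominal 5% per factor | rho 0.3 | rho 0.5 | rho 0.7 |
|---|---|---|---|
| ANOVA, per factor | 2.7% | 3.4% | 3.9% |
| ANOVA, either factor | 5.4% | 6.7% | 7.6% |
| ANCOVA, either factor | 9.7% | 10.0% | 9.5% |
| ANOVA or ANCOVA, either factor | 10.7% | 11.2% | 10.7% |
| Any of three models, either factor | 12.1% | 12.5% | 11.8% |

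Repeat runs differ by a few tenths of a point; about 2.8–4.1% is a fair statement of the ANOVA per-factor rate. At 0.025 per factor, the ANCOVA alone gives 4.8–5.1%. Allowing any of the three models gives 6.0–6.6%.

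**Step 4: a limit on step 2.** The 79% takes the ANOVA's reported standard error at face value. Under stratification the true spread is smaller. At rho = 0.5 an error rate of 3.4% implies a ratio of 1.96/2.12 = 0.92. Power is then about Φ((0.398 × √(118.75/2) − 2.24)/0.92) = Φ(0.83/0.92), or about 82% by this normal approximation, which gives 80% without the correction. The ANOVA is thus a point or two better than tabled, and the ANCOVA's advantage correspondingly smaller.

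**The case against.** The strongest reply has four parts.

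- **The adjusted analysis is already planned.** This is true. Reporting unadjusted, adjusted and expanded models in turn is common, and 2.6.2 defines the main outcome as a change, so the ANOVA can be read as the lead analysis. But the text never says so. If it is the lead, the plan rests on the less precise model and the one it describes as potentially biased.
- **Power is not lost against plan.** This stands. The trial was sized with a t-test, which corresponds to the unadjusted comparison, and about 79% at 0.025 is essentially the planned 80%. A reader might infer that the trial is underpowered; the documents do not support that.
- **The error rate is easily overstated.** This also stands. A reader might count two factors times three models as six chances at 5%, which would be 26% if independent. The models share patients, outcome and contrasts, so the tests are strongly correlated. Nor does 9.75% (two independent tests at 5%) describe the ANOVA here, because ignoring the strata makes it conservative.
- **Bonferroni is mentioned, 95% intervals do not exclude adjusted tests, and the full protocol and SAP may settle the level.** In part. It would be wrong to say that multiplicity is ignored. What remains is that the article uses the adjustment to help justify recruitment and then describes the primary analysis without it.

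**Conclusion.** The point holds as an inconsistency that should be fixed; it does not invalidate the trial. Section 2.7.2 gives three models for one endpoint without a deciding one, lists first the model that omits both stratification factors, and does not carry over the adjustment behind part of the increase to 250.

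- **Precision.** The ANCOVA gains about 15 points of power at rho = 0.3 and about 2 at rho = 0.9, slightly less once stratification is allowed for. The direction is certain for rho below 1 with equal variances. The size rests on an undocumented correlation and on the assumption that 200 gives 80%.
- **Error rate.** For rho of 0.3 to 0.7 at 5% per factor, familywise error is about 5.5–8% for the ANOVA alone, about 10% for the ANCOVA alone, and 11–13% if any model may be cited. Most of this comes from testing two factors at 5%; free choice of model adds only about 2–3 points to the ANCOVA figure. The contribution of the third model depends on assumed covariates and an assumed selection threshold, which the article does not specify.

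**What to change.** In section 2.7.2:
- Name one primary analysis: the ANCOVA of week-4 mNRS on THC, CBD, continuous baseline mNRS and sex, which the section already describes. Its treatment coefficients are the same as those from regressing change on the same terms, so the main outcome in 2.6.2 is unaffected.
- Test each factor at 0.025, with 97.5% intervals as the decision intervals, or use Holm and state how intervals will be presented. State in 2.7.1 that the Bonferroni adjustment is for these two tests, if that is what was intended.
- Label the change-score ANOVA and the expanded ANCOVA as supportive, with no claim resting on them.

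The cost is wording only, with no new data or visits. Decision intervals become wider than 95% intervals from the same model, by 2.24/1.96 = 1.14 (about 14%). Section 2.1 reports 41 randomized by 29 May 2024, and section 2.7 defers analysis until all randomized subjects have completed, so on the article's account the change can be made before the treatment comparison is seen.

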## Abstract

**Background:**

Multiple sclerosis (MS) is an inflammatory and degenerative disease of the central nervous system. More than 90,000 Canadians are affected; a cure is yet to be found. Available treatments to manage the disease course are only partially effective. For many years, persons with MS (PwMS) have used cannabis to relax, to reduce pain and spasticity, or to improve sleep and daily functioning, despite the lack of scientific evidence on the efficacy of specific cannabinoids [i.e., tetrahydrocannabinol (THC) and cannabidiol (CBD)] on these MS symptoms. The purpose of this clinical trial is to assess the effectiveness of different doses of these cannabinoids, alone or combined, on spasticity relief, compared to placebo. Moreover, we aim to determine which treatment is best effective to address other key MS conditions.

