### Hypothesis

1.1

We hypothesize that the administration of different doses of THC alone, CBD alone, and THC and CBD combined will result in a significant relief of spasticity compared to placebo.

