### Study objectives

1.2

The main aims of this study are: (1) to compare the efficacy of THC and CBD, alone and in combination, as add-on therapies to the current standard treatments for relief of spasticity in PwMS, (2) to assess the tolerability profile of THC and CBD, alone and in combination, (3) to identify the mechanisms underlying such therapeutic and adverse effects, considering sex, age, pharmacology, and immune profile.

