#### Secondary and exploratory endpoints

2.7.3

The secondary and exploratory outcomes will be analyzed using the same methods as spasticity. Exploratory outcomes and mechanistic factors (sex, neurobiological markers, age, etc.) will be analyzed using ANCOVA models.

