## Discussion

3

Current therapeutic approaches for MS have partial efficacy. Disease-modifying therapies are limited in their action on MS symptoms (11). Both preclinical and clinical data support that analgesic, antihyperalgesic, neuroprotective, and anti-inflammatory properties have been attributed to cannabis-derived cannabinoids, essentially THC and/or CBD (30, 80). The CANSEP trial is part of a large Canadian Institutes of Health Research program on cannabis research in priority areas (21). It was developed in response to the lack of evidence about the safety and the efficacy of specific cannabinoids in MS (20). The originality of our study comes from the fact that we will compare the distinct and combined effects of THC and CBD on spasticity and other symptoms such as pain, sleep, well-being, and quality of life of Canadian PwMS.

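### The article aims to compare THC with CBD and to find the best treatment for other MS symptoms, but no stated efficacy analysis estimates one drug against the other

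*Protocol article*

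**What the plan says.** **Aims.** The first aim in 1.2 is "to compare the efficacy of THC and CBD, alone and in combination, as add-on therapies to the current standard treatments". That sentence names no comparator. The Abstract (Background) first describes a comparison with placebo for spasticity and then adds a separate purpose: "we aim to determine which treatment is best effective to address other key MS conditions". The Introduction gives CBD versus THC as the open question. The Discussion presents as the study's originality that "we will compare the distinct and combined effects of THC and CBD on spasticity". The hypothesis in 1.1 is narrower: each active regimen "will result in a significant relief of spasticity compared to placebo".

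**Efficacy analyses.** In 2.7.2, "The ANOVA model will only include the factors THC and CBD". The two ANCOVAs that follow add baseline score, sex and possible confounders. On reporting, "The estimated adjusted and unadjusted differences in mNRS from baseline to week 4 and their 95% confidence intervals will be reported for all models", but which differences are meant is not said. For the other symptoms, 2.7.3 states: "The secondary and exploratory outcomes will be analyzed using the same methods as spasticity". Section 2.7.6 adds a model with the THC-by-CBD interaction, as a sensitivity analysis only.

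**Sample size.** Section 2.7.1 seeks at least 80% power at two-sided 5% for the effects of the two factors. It arrives at 200 patients, raised to 250 for a Bonferroni adjustment and 5% attrition.

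**Safety.** Section 2.7.3.2 plans relative and absolute adverse-event risks between arms.

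**The concern.** An additive two-factor model answers two questions: does THC do better than no THC, and does CBD do better than no CBD? Asking which drug is better, or whether the combination beats either drug alone, is a comparison among active treatments. A statement about the best treatment cannot rest on tests against absence or placebo.

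The combination has a further difficulty. The additive model sets its effect to the sum of the two drug effects. If both estimates are favourable, the combination ranks first by assumption, and that ranking is never tested.

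At stake is the guidance the Discussion promises to patients and clinicians. With no contrast named, the readily available basis for a ranking is to see which factor reached significance. That does not test a difference. Because 2.7.3 carries the same methods over to every secondary symptom, the gap recurs exactly where the best-treatment purpose sits.

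**Working it through.** **1. Which efficacy comparisons the stated models name**

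| Question | Named analysis |
|---|---|
| THC vs no THC | Factor effect, 2.7.2 |
| CBD vs no CBD | Factor effect, 2.7.2 |
| Are the effects additive? | Interaction, 2.7.6 (sensitivity) |
| THC vs CBD | None |
| Combination vs each drug alone | Only as the other drug's factor effect, under additivity |

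**2. The plan's own figure.** The 200 cannot be reproduced, because 2.7.1 gives neither a standard deviation (SD) nor a placebo change. Working back from two-sided 5% and 80% power:
- Factor margins (100 vs 100) imply a standardised effect of 0.398 SD.
- For a treated change of -1.55 and an assumed placebo change of 0 to -1.0, the implied SD is 1.55/0.398 = 3.89 down to 0.55/0.398 = 1.38 points.
- The step to 250 reproduces with two Bonferroni tests: 242.4/0.95 = 255.1, within 3% of 250. Three tests give 267.1/0.95 = 281.1, which does not. The number of tests is not stated, so two is an inference.

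**3. Equal drugs, exactly one factor significant.** In the balanced 2x2 design the two factor estimates are uncorrelated. With power p for each, the chance that exactly one is significant is 2p(1-p).

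| Power | 2p(1-p) |
|---|---|
| 90% | 18% |
| 85% | 25.5% |
| 80% | 32% |
| 70% | 42% |
| 50% | 50% (the maximum) |

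At 0.398 SD with 250 x 0.95 = 237.5 analysed:
- Alpha 0.025: power 79.1%, so 2 x 0.791 x 0.209 = 33%.
- Alpha 0.05: power 86.3%, so 2 x 0.863 x 0.137 = 24%.

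Simulation of the additive model (236 patients, 40,000 trials per scenario) gave 33.7% and 24.0%. The direct contrast at the 5% level was falsely significant in about 5% of the same trials.

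**4. Precision of the direct contrast.** With N analysed in equal arms:
- Var(factor effect) = 4 SD²/N.
- Var(THC effect minus CBD effect) = 4 SD²/N + 4 SD²/N = 8 SD²/N.
- Ratio of standard errors = √2 = 1.41.
- Combination vs a single drug in the four-arm model compares two arms of N/4, so its variance is also 8 SD²/N.

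With N = 237.5, the standard error of the contrast is √(8/237.5) = 0.184 SD. Its power is about 58% for a gap of 0.398 SD and about 19% for half that gap. A gap of 0.51 SD is needed for 80% power, against 0.36 SD for a factor effect.

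**5. Sensitivity to the assumptions**
- With all 250 analysed, power for a gap of 0.398 SD is about 60%, before any dilution from baseline-value imputation.
- If the 200 had been sized on single arms (50 vs 50), the implied effect would be 0.566 SD. Factor power at alpha 0.025 would then be about 98%, and 2 x 0.982 x 0.018 = 3.5%. The contrast would have about 87% power for a gap of that size. Section 2.7.1 speaks of the two factors, so the margins reading is used here.

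**The case against.** **The first aim may mean versus placebo.** The hypothesis, the Abstract's sentence on spasticity and the Discussion all frame the regimens against placebo, and power was set for the factor effects. This stands for spasticity: 1.2 is open to that reading. It does not stand for the Abstract's purpose of finding the best treatment for other conditions, which can only be a comparison among treatments. Nor may the two statements be merged: a reader might take the best-treatment purpose as part of the first aim, but it appears only in the Abstract and does not concern spasticity.

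**The model does not prevent the comparison.** True. THC minus CBD is a linear contrast of two fitted coefficients, and the reporting sentence in 2.7.2 does not exclude it. A condensed article may also leave contrast lists to the full protocol. But this article fixes the model terms, the covariates, the sensitivity model and the powered effects, and together these do not match a stated purpose.

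**No rule ranks drugs by significance.** Also true. A reader might infer that the plan will declare a winner from two p-values, but nothing says so, and estimates with intervals are promised. The error rates above describe a risk of interpretation that the plan leaves open.

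**Drugs are compared elsewhere.** Adverse-event risks are compared between arms, and an interaction model is planned. A claim that THC and CBD are never compared would be too broad; it holds for efficacy. The interaction model tests additivity, not THC against CBD, though it can supply the combination contrasts.

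**Conclusion.** The point holds in limited form. The stated efficacy analyses do not include the comparison among active treatments that the article sets as a purpose. The contrast is estimable but neither specified nor powered. The combination's standing rests on additivity, unless the sensitivity model is used for it.

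Size: if readers inferred a difference from one significant and one non-significant factor, equally effective drugs would appear to differ in about a quarter to a third of trials at the planned power. A third is not an upper bound, since the rate reaches 50% at 50% power and falls when power is high. This rests on equal true effects, 0.398 SD back-solved for factor margins, and about 237 analysed. Under the same assumptions a direct contrast has roughly 58% power for a gap of 0.398 SD, so the trial can offer a head-to-head estimate of modest precision. The ratio of 1.41 needs only balanced arms and a common SD.

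The primary tests and the sample size for the factor effects are not affected. The change should be made, but it does not threaten the main analysis.

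**What to change.** Add to 2.7.2, and by reference to 2.7.3:

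*From the baseline-adjusted model we will estimate the THC effect minus the CBD effect with its 95% confidence interval. From the model with interaction (2.7.6) we will estimate the combination against THC alone and against CBD alone, with 95% confidence intervals. These are secondary estimates. A treatment will be described as better or best only on the basis of such a contrast.*

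State beside it that the head-to-head contrast has a standard error about 1.41 times that of a factor effect and that the sample size was not set for it. Do not quote a half-width in SD units or scale points as a protocol figure: the article gives no SD, and any such number would come from a back-solved, unadjusted assumption. Bring the Abstract's wording on the best treatment into line with what these contrasts can support.

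Cost: a few contrast lines from models already planned, plus wording. No patients, visits or changes to the primary tests. Section 2.7 places the analysis after all randomised subjects have completed, so the addition can be fixed beforehand. The downside is that the plan must admit limited precision for the head-to-head comparison.
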